**Fig. 1 Fig1:**
[figure not shown]
Study design of the INTER-ACT randomised controlled trialᅟ

#### Mobile application

The mobile app runs throughout the intervention periods and consists of four domains: nutrition, physical activity, weight, and mental wellbeing. In the nutrition domain, the participant sets nutrition goals based on the Belgian ‘active food triangle’ [34]. If applicable, the nutrition goals are adapted for lactating or pregnant women. On a daily basis, the participant can indicate whether or not she achieved her nutrition goal. In the physical activity domain, the participant sets a goal regarding the number of steps she wants to achieve every day. A Bluetooth-connected activity and sleep tracker (Withings GO™) registers the participant’s activity and sleep, and allows the app to assess whether the physical activity goal is reached. Weight is recorded by a Bluetooth-connected weighing scale (Body Cardio Withings™). In the mental wellbeing domain, the participant can indicate her mood by choosing one out of five emoticons that express different mood states. Besides, the participant can indicate her stress level on a stress meter in the shape of a thermometer. Custom made tips are sent to support the participant in achieving her nutrition and physical activity goals. Additionally, based on the participant’s progress and mood state, the app sends positive coaching messages in order to further motivate the participant. The app development and pilot study of the app including results from evaluation questionnaires will be described in a subsequent paper.

### Ensuring adherence

Adherence to the intervention is enhanced in several ways. Firstly, the coaching sessions coincide with the postnatal follow-up visit and government vaccine scheme (in the interpregnancy phase) and routine ultrasound scans during the 1^st^, 2^nd^ and 3^rd^ trimester of pregnancy (in the new pregnancy phase) in order to reduce barriers to attend the sessions. Secondly, the participants can choose the study location of their preference: at the hospital, private clinic, ‘Child & Family’ organisation, or at the home of the participant. Thirdly, between the two intervention phases, adherence to physical activity and healthy nutrition behaviour are stimulated by sending 3-monthly motivational coaching messages to the participant.

### Participant timeline

Women are recruited at day 2 or 3 postpartum. Coaching sessions take place at week 6, week 8, week 12 and month 6 postpartum. Subsequently, coaching sessions take place before week 15, week 20 and week 35 in the next pregnancy. The mobile app is used from week 6 to month 6 postpartum and in the next pregnancy (Fig. 1).

### Outcomes

In this RCT, we aim to evaluate a composite outcome as primary outcome, of which at least one of the following outcomes occurs in the subsequent pregnancy:Pregnancy-induced hypertension (PIH): new-onset elevations of blood pressure (systolic blood pressure > 140 mmHg and diastolic blood pressure >90 mmHg) after 20 weeks of gestation without significant proteinuria [35].Gestational diabetes mellitus (GDM): is defined as any degree of glucose intolerance with onset or first recognition during pregnancy [36]. GDM is diagnosed at 24–28 weeks of gestation with the two steps screening strategy which consists of a 50 g glucose challenge test (GCT) and a 2-h 75 g oral glucose tolerance test (OGTT). GDM is diagnosed upon an abnormal GCT (≥ 140 mg/dl) followed by an abnormal OGTT (≥ 153 mg/dl) based on the VDV-VVOG-Domus Medica consensus 2012 and IADPSG criteria [37].Caesarean section (CS): surgical procedure in which a foetus is delivered through an incision in the mother’s abdomen and uterus.Large-for-gestational-age baby (LGA): birth weight >90^th^ percentile on Flemish sex- and parity-adjusted growth charts [38].

Secondary outcomes are the following:Maternal weightBody compositionBlood pressureBreastfeedingFood intakePhysical activityLifestyle behaviourQuality of lifeMental wellbeing

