## Background

Maternal pre-pregnancy weight is related to pregnancy- and birth outcomes. An excessive weight before conception increases the risk for pregnancy- and birth related complications such as gestational diabetes mellitus (GDM), pregnancy-induced hypertension (PIH), caesarean section (CS), or a large-for-gestational age (LGA) infant [1–4]. Besides, excessive gestational weight gain (EGWG), i.e. a gestational weight gain (GWG) higher than the recommended GWG by the Institute Of Medicine (IOM) [5], is also associated with these perinatal complications [6–8]. Both the pre-pregnancy BMI and gestational weight gain (GWG) are thus considerable risk factors of pregnancy and birth complications. Between 2009 and 2014, the Flanders Study centre Perinatal Epidemiology (SPE) collected data of almost 400.000 singleton pregnancies in Flanders, Belgium, on the combined association of GWG and pre-pregnancy BMI with the prevalence of the composite outcome of pregnancy and birth complications (i.e. at least one of four perinatal outcomes PIH, GDM, CS and/or LGA infant). The prevalence of the composite perinatal outcome was 26% in women with a normal BMI and an adequate GWG; 34% in women with a normal BMI but with an excessive GWG; and 66% in women with class III obesity (BMI ≥ 40) and excessive GWG [SPE, 2016 in progress]. A Norwegian study reported similar findings. Haugen et al. [9] found that normal weight and overweight women with EGWG had an increased risk for PIH, preeclampsia, CS, high birth weight (>4500 g) and LGA infant. Moreover, women of all BMI classes and with EGWG, except underweight women, had an increased risk of more than 2 kg postpartum weight retention (PPWR) at 18 months postpartum [9]. Conversely, a more recent study from Xiong et al. reported an increased likelihood of CS in underweight or normal weight women with EGWG compared to overweight or obese women EGWG [10]. Thus, these results highlight the importance of adequate GWG in all BMI groups.

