### Sample size

The primary endpoint is the composite endpoint of selected pregnancy- and birth-related complications: PIH, GDM, CS and LGA. PIH and GDM are assessed during pregnancy; CS and LGA are determined at time of delivery (Fig. 1). In order to find a significant difference between the intervention and control arm in the rate of the selected pregnancy- and birth-related complications (composite endpoint), assuming a 42% complication rate in the intervention arm and 30% in the control arm (1/4 relative reduction), with a statistical power of 80% and significance level of 0.05, we need 500 women with a next (second) delivery: 250 women in the intervention arm and 250 women in the control arm.

The figures for mean duration between birth and start of a new pregnancy vary around 18 to 24 months. We assume that 2/3 of the included women have a next delivery within 3 years since inclusion in the trial. We also take into account a 30% drop-out rate during follow-up till end of the next pregnancy. In order to obtain 500 women with a next delivery, taking into account a 30% drop-out and only 65% having a next pregnancy within 3 years, we need to include 500x(1/0.65)x(1/0.7) = 1100 women: 550 women per arm.

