#### Medical record data

Data from the medical record comprise pre-pregnancy weight, pregnancy weight gain, pregnancy- and birth outcomes, data of the new-born such as birthweight and LGA, familial medical history (familial type 2 diabetes mellitus, familial hypertension), chronic disease, psychological history; comorbidity; use of medication; medical history of (previous) pregnancy (GCT, OGTT, GDM, PIH, CS, proteinuria (>300 mg/24 h), preeclampsia, preterm delivery (<37 weeks of gestation) and miscarriage).

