### Statistics

All analyses will be carried out using the intention-to-treat principle with data from all participants enrolled in the study. The statistical software SAS version 9.4 will be used. Descriptive statistics for baseline values in the two arms will be presented. There will be no tests of statistical significance or confidence intervals for differences between the two arms, as these are randomised groups. The drop-out rate will be assessed and compared between the two arms. The composite endpoint consists of occurrence of at least one of the following four major pregnancy and birth related complications, at time of next pregnancy: PIH, GDM, CS, and LGA. The rate of the composite endpoint will be calculated and 95% confidence intervals provided in intervention and control arm: 1) in all included patients (intent-to-treat), 2) in all patients completed a next pregnancy. If drop-out rates, reason for drop-out, next pregnancy rates differ between the intervention arm and control arm, the rate of the composite endpoint in patients with a next pregnancy has to be interpreted carefully.

A full statistical analysis plan will be written by the trial statistician prior to any analysis being undertaken. We will report data in line with the Consolidated Standards of Reporting Trials (CONSORT) 2010 Statement [54] and a *P*-values <0.05 will be considered statistically significant.

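### The hypertensive component of the primary composite excludes hypertension with significant proteinuria, so preeclampsia has no place of its own in the endpoint; separately, it requires both pressures to be raised

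*Protocol article*

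**What the plan says.** **Component definition (Outcomes).** Pregnancy-induced hypertension (PIH) is new-onset raised blood pressure, specified as "systolic blood pressure > 140 mmHg and diastolic blood pressure >90 mmHg) after 20 weeks of gestation without significant proteinuria", with reference [35] cited.

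**Composite rule (Statistics).** The endpoint is the "occurrence of at least one of the following four major pregnancy and birth related complications, at time of next pregnancy: PIH, GDM, CS, and LGA". All four items are named again in the Abstract, Outcomes and Sample size sections. Preeclampsia is not among them, nor among the secondary outcomes, which include blood pressure as a measurement but no hypertensive diagnosis.

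**Data items (Medical record data).** PIH, proteinuria and preeclampsia are listed separately: "medical history of (previous) pregnancy (GCT, OGTT, GDM, PIH, CS, proteinuria (>300 mg/24 h), preeclampsia".

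**Rationale (Background).** A Norwegian study is cited as finding that "normal weight and overweight women with EGWG had an increased risk for PIH, preeclampsia, CS" and other complications, again with PIH and preeclampsia as two items.

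**The concern.** The composite is meant to capture complications related to weight and gestational weight gain. As written, its hypertensive part admits the form without proteinuria and shuts out the form with it, and nothing elsewhere brings the second form back. The article does not use PIH loosely as an umbrella term, because its rationale and its data list both keep preeclampsia apart.

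Three groups of women are affected:

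- **Hypertension with significant proteinuria from the outset.** These women do not meet the component.
- **PIH first, proteinuria later.** No rule says whether the earlier state or the final diagnosis decides. The Randomisation section states that there is no blinding, so this choice should not be left to whoever scores the record.
- **Only one pressure above its limit.** A reading of 165/88 mmHg after 20 weeks fails the definition because the diastolic value is not above 90. This is a second, independent point and has nothing to do with proteinuria.

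At stake is whether the primary endpoint measures what it is said to measure.

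**Working it through.** **1. Reading the rule.** A woman with new hypertension after 20 weeks and significant proteinuria is scored as follows.

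| Component | Met? |
|---|---|
| PIH | No, because of the proteinuria exclusion |
| Gestational diabetes | Only if diagnosed |
| Caesarean section | Only if performed |
| Large-for-gestational-age infant | Only if birth weight is above the 90th percentile |

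She is a composite event only through one of the last three rows.

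**2. The planned figure.** The Sample size section plans "assuming a 42% complication rate in the intervention arm and 30% in the control arm (1/4 relative reduction"), for 80% power at the 0.05 level, and arrives at 250 women per arm. Using the two rates as printed, with a two-sided test (sidedness is not stated), pooled variance and no continuity correction:

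n per arm = [1.960 × √(2 × 0.36 × 0.64) + 0.842 × √(0.42 × 0.58 + 0.30 × 0.70)]² / 0.12² = 250

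Power at 250 per arm is 0.800, so the stated figure reproduces. Planned events are 250 × 0.42 + 250 × 0.30 = 105 + 75 = 180, and the planned difference between arms is 30 events.

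**3. Women misclassified.** The article gives no preeclampsia rate and no overlap with the other components. Assume preeclampsia in 2% to 5% of next pregnancies, with half of the cases not otherwise counted:

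- Low end: 0.02 × 0.5 = 1%; 500 × 0.01 = 5 women.
- High end: 0.05 × 0.5 = 2.5%; 500 × 0.025 = 12.5, or about 12 women.

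With wider assumptions (1% to 5% affected, 30% to 70% of them already counted), the uncounted share m runs from 0.01 × 0.3 = 0.3% to 0.05 × 0.7 = 3.5%. That is about 0.8 to 8.7 women per 250.

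**4. Effect on power at 250 per arm.** This arises only if the planning rates were meant to include preeclampsia, which the article does not say. Two patterns of loss are shown: proportional to the arm rates (0.42 − m against 0.30 − m × 30/42), and equal in both arms (0.42 − m against 0.30 − m).

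| Uncounted share m | Proportional loss | Equal loss |
|---|---|---|
| 0.3% | 0.796 | 0.801 |
| 1.0% | 0.785 | 0.805 |
| 2.5% | 0.762 | 0.813 |
| 3.5% | 0.745 | 0.819 |

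Under equal loss the difference of 12 percentage points is kept and the variance shrinks, so power does not fall.

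**5. The *and*.** The share of women with only one pressure raised cannot be derived from the article. No figure is offered.

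**The case against.** **The composite is a deliberate selection.** The Sample size section calls the complications selected, the same four appear throughout, and the regional registry composite in the Background uses the same four labels. The sentence naming preeclampsia reports a different, Norwegian study and does not contradict the composite. This stands in part. There is no formal contradiction, and a wider component could reduce comparability with the registry, whose PIH definition is not shown. But choosing four labels does not explain why the proteinuric form should count as no hypertensive complication.

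**A reader might infer that every woman who develops preeclampsia is scored as free of complications.** The text does not support that. She can count through the other three components, and a woman who had PIH before proteinuria appeared may already count, because the composite asks only that an outcome occurs.

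**A reader might also infer that an intervention preventing progression from PIH to preeclampsia adds events to its own arm.** That needs a rule by which later preeclampsia cancels earlier PIH. The article states none, so the argument falls.

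**The *and* may be a condensing slip.** The full protocol and reference [35] are not shown. This is fair, and is why the request is to reconcile it. It also plays no part in the preeclampsia exclusion.

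**The data may not be at hand.** Medical record data lists preeclampsia under previous pregnancy. However, the same section covers pregnancy and birth outcomes, and Time of data collection has the record consulted again at the end of the subsequent pregnancy. Availability is likely but not explicit.

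**Conclusion.** The point holds as a badly fixed rule in the primary endpoint. It is not detail left to an analysis plan, because the article sets explicit thresholds and an explicit exclusion. Hypertension with significant proteinuria from the outset is not counted in its own right, progression from PIH is ambiguous, and the conjunction of pressures is a distinct wording problem.

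The size is modest and rests on assumptions: about 5 to 12 of 500 women if 2% to 5% are affected and half are otherwise uncounted. Over the wider range, power would lie between 0.796 and 0.745 under proportional loss, and would not fall under equal loss. It would be wrong to conclude that the treatment comparison is shown to be biased or that the trial is materially underpowered on this account. The reason to act is the validity of the endpoint, at little cost.

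**What to change.** Before any between-arm comparison, and at the latest in the analysis plan that the Statistics section promises:

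1. Define the component as any new-onset hypertensive disorder after 20 weeks, with or without proteinuria: PIH or preeclampsia, including PIH that progresses. Report PIH and preeclampsia separately.
2. Keep the four-item composite as published as a sensitivity analysis.
3. Reconcile the *and* between the two pressures with the article's reference [35], and state how an isolated systolic or diastolic elevation is scored.
4. Confirm whether the 42% and 30% planning rates and the regional registry composite rest on the same definition.
5. Confirm that preeclampsia and proteinuria are extracted from the medical record for the subsequent pregnancy.

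**Cost.** An amendment to the outcome definition, a small departure from the published composite, and possibly some loss of comparability with the registry. New data collection is probably unnecessary, subject to item 5.

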### Sample size

The primary endpoint is the composite endpoint of selected pregnancy- and birth-related complications: PIH, GDM, CS and LGA. PIH and GDM are assessed during pregnancy; CS and LGA are determined at time of delivery (Fig. 1). In order to find a significant difference between the intervention and control arm in the rate of the selected pregnancy- and birth-related complications (composite endpoint), assuming a 42% complication rate in the intervention arm and 30% in the control arm (1/4 relative reduction), with a statistical power of 80% and significance level of 0.05, we need 500 women with a next (second) delivery: 250 women in the intervention arm and 250 women in the control arm.

The figures for mean duration between birth and start of a new pregnancy vary around 18 to 24 months. We assume that 2/3 of the included women have a next delivery within 3 years since inclusion in the trial. We also take into account a 30% drop-out rate during follow-up till end of the next pregnancy. In order to obtain 500 women with a next delivery, taking into account a 30% drop-out and only 65% having a next pregnancy within 3 years, we need to include 500x(1/0.65)x(1/0.7) = 1100 women: 550 women per arm.

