## Discussion

Excessive weight before and during pregnancy is a public health threat since it may lead to pregnancy- and birth related complications such as pregnancy-induced hypertension, gestational diabetes mellitus, caesarean section, and large for gestational age infants in the short term and weight-related chronic diseases in the long run. Moreover, maternal obesity may lead to inter-generational cycles of obesity through intra-uterine programming of the foetus. Therefore it is essential to timely implement lifestyle interventions targeting high-risk groups.

INTER-ACT is a unique lifestyle intervention that focuses on weight, diet, physical activity and mental well-being between pregnancies and during a subsequent pregnancy with the aim to reduce pregnancy- and birth related complications. The intervention especially focuses on those who are most at risk of these complications in a subsequent pregnancy: women with excessive gestational weight gain during their previous pregnancy.

Strengths of this study can be found in 1) the design of this e-health driven randomised controlled trial, 2) the six participating study sites that represent the northern population of Belgium, and 3) the large sample size calculated as such to demonstrate differences between intervention and control group. A potential pitfall of this study is the long follow-up, i.e. until the end of the subsequent pregnancy, which might result in high drop-out rates. However, possible drop-outs were considered in the power calculations for the needed sample size. This study therefore has the strong potential to show the effectiveness of the e-health driven coaching program for women between and during pregnancies to obtain a healthy lifestyle, to achieve a healthy weight, and to reduce pregnancy- and birth related complications.

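### The sample-size sentence reverses the arm labels and calls a 28.6% reduction a quarter; 250 per arm has 80% power for 42% versus 30%, but about 68% for a true quarter reduction from 42%

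*Protocol article*

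**What the plan says.** The Sample size section of the protocol article gives the planning assumptions for the primary endpoint in one sentence. The rates are introduced as "assuming a 42% complication rate in the intervention arm and 30% in the control arm (1/4 relative reduction"), followed by "with a statistical power of 80% and significance level of 0.05". The conclusion is "we need 500 women with a next (second) delivery: 250 women in the intervention arm and 250 women in the control arm". The next paragraph inflates the 500 deliveries for women without a further pregnancy (65% expected to have one) and for 30% drop-out, which gives 1100 women enrolled.

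The rates appear nowhere else in the article, so nothing corrects them. The direction of the expected effect is clear from the Discussion, which says that the intervention is meant to lower these complications. The Discussion also counts as a strength "the large sample size calculated as such to demonstrate differences between intervention and control group".

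**The concern.** Three elements of the sentence do not fit together: the arm labels, the relative effect and the sample size.

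- **Direction.** Read literally, the planning hypothesis is that coaching raises the composite rate from 30% to 42%. That contradicts the word for a decrease in the same parenthesis, and the purpose of the trial.
- **Size of effect.** Exchanging the labels restores the direction but not the arithmetic, because a fall from 42% to 30% is larger than a quarter.
- **Power.** If the number of women comes from the two rates, the trial is sized for a larger effect than the one named in words. Anyone who takes "1/4 relative reduction" as the target will credit the trial with 80% power that it does not have for that effect.

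This is the article's only statement of the planning hypothesis for the primary endpoint. It also fixes the assumed control rate, which is the figure one would later compare with the observed rate to judge the planning. As printed, that figure is "30% in the control arm", whereas the aim of the trial implies 42%.

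**Working it through.** **Inputs, all from the Sample size section:** rates 0.42 and 0.30; power 0.80; "significance level of 0.05"; "250 women in the intervention arm and 250 women in the control arm", so 1:1 allocation. Sidedness is not stated. I assume two-sided and test that assumption in step 3.

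**1. Relative effect.**

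- As printed (control 30%, intervention 42%): (42 − 30)/30 = 40% relative increase.
- Labels exchanged (control 42%, intervention 30%): (42 − 30)/42 = 28.6% relative reduction.
- A quarter off 42% is 0.75 × 42% = 31.5%.
- A quarter reduction ending at 30% starts from 30%/0.75 = 40%.

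**2. Reproducing the plan's figure.** The pooled-variance formula for two proportions, without continuity correction, is

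n per arm = [z(0.975)·√(2·p̄·(1 − p̄)) + z(0.80)·√(p1(1 − p1) + p2(1 − p2))]² / (p1 − p2)²

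with z(0.975) = 1.960, z(0.80) = 0.842 and p̄ the mean of the two rates. For 0.42 and 0.30, p̄ = 0.36:

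- 2 × 0.36 × 0.64 = 0.4608, square root 0.6788
- 0.42 × 0.58 + 0.30 × 0.70 = 0.4536, square root 0.6735
- n = (1.3305 + 0.5668)² / 0.12² = 3.5997/0.0144 = 249.98

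This rounds up to 250 per arm, exactly as stated. Exchanging the labels does not alter it, because the formula is symmetric in the two rates. The unpooled variant gives 248.

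**3. Sidedness.** A one-sided 5% test for 42% versus 30% would need 197 per arm (214 with continuity correction). A one-sided test for a true quarter reduction would need 260 (42% versus 31.5%) or 281 (40% versus 30%). None of these is 250, so the stated number points to a two-sided test of 42% versus 30%.

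**4. Power of 250 per arm for a true quarter reduction.** From the same approximation,

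power = Φ{ [|p1 − p2|·√n − 1.960·√(2·p̄·(1 − p̄))] / √(p1(1 − p1) + p2(1 − p2)) }

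- 42% versus 31.5%: (0.105 × 15.811 − 1.3364)/0.6778 = 0.478, so power is 68.4%.
- 40% versus 30%: (0.10 × 15.811 − 1.3221)/0.6708 = 0.386, so power is 65.0%.

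**5. Summary, two-sided 0.05.** Enrolment uses the article's own inflation, deliveries/(0.65 × 0.7).

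| Control vs intervention | Relative reduction | Power at 250 per arm | Per arm for 80% | Deliveries | Enrolled |
|---|---|---|---|---|---|
| 42% vs 30% | 28.6% | 80.0% | 250 | 500 | 1099 (stated as 1100) |
| 42% vs 31.5% | 25% | 68.4% | 330 | 660 | 1451 |
| 40% vs 30% | 25% | 65.0% | 356 | 712 | 1565 |

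**The case against.** The strongest reply is that no design quantity is wrong. Two explicit rates, 80% power and a 5% level give exactly 250 per arm, and both 500 deliveries and 1100 enrolled follow from that. The reversed labels are an evident slip that changes neither the number nor the test. The quarter is most naturally a loose gloss on the two rates; on that reading, power for the planned effect is 80% as claimed, and the 68% answers a question the authors did not pose. The 68% also depends on a two-sided test; one-sided it would be 78.7%. Finally, the Statistics section plans composite rates with 95% confidence intervals by arm, so a null result would not be judged on the parenthesis alone, and the Discussion sentence repeats none of the wrong figures.

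Much of this stands. The sample size is right for 42% versus 30%, the power shortfall applies only if a quarter is the real target, and the two-sided test is an inference. The Discussion sentence relies on the calculation but is not a second instance of the error.

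The errors themselves remain. The gloss is not harmless rounding: 28.6% does not round to 25%, and the gap is worth about 12 points of power (80.0% against 68.4%). Nor is this a detail left to an analysis plan, since the article states the direction and the relative size of the effect wrongly.

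**Conclusion.** The sentence is wrong as written in two respects: the arm labels are reversed, and the effect is 28.6% rather than a quarter. The 250 per arm is correct for 42% in the control arm and 30% in the intervention arm, with 80.0% power.

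For a true quarter reduction, 250 per arm gives 68.4% power if the control rate is held at 42%, or 65.0% if the intervention rate is held at 30%. The type II error is then 32% to 35% instead of 20%. These figures assume a two-sided 5% test without continuity correction, equal arms, and 250 evaluable deliveries in each arm. The document does not say whether the rates or the quarter express the intended target, but its sample size matches the rates.

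**What to change.** The sponsor should confirm the intended target and rewrite the sentence accordingly.

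- **If the two rates are the target:** state 42% for control and 30% for intervention, a difference of 12 percentage points or a 28.6% relative reduction, with 250 deliveries per arm, 80% power and a two-sided 0.05 level. This changes wording only. Enrolment stays at 1100.
- **If a quarter reduction is the target and the size is kept:** give the matching pair of rates and restate the power of 500 deliveries as 68% (42% versus 31.5%) or 65% (40% versus 30%). No participants are added, but the stated power is less favourable.
- **If a quarter reduction and 80% power are both required:** 660 or 712 deliveries are needed. With the article's inflation that means about 1451 or 1565 women enrolled, which is 351 or 465 more than 1100.

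In each case, say explicitly that the test is two-sided. The Discussion's claim about the sample size should then be read against the corrected target.
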